Study aims.Aim 1: Describe subscriber losses at different points during pregnancy and postpartum period from the programObjective 1a. Determine differences in subscribers who remain subscribed to Kilkari throughout the duration of service versus those lost at different points along the continuum of program databases.Objective 1b. Develop a classifier for identifying different categories of losses.Aim 2: Facilitate the program’s ability to identify and target ASHAs likely to perform poorly on digital health training programs and knowledge assessmentsObjective 2a. Determine predictors of training course completion (overall and time to completion) by ASHAs based on performance on early modules of the course and other characteristics including reported motivation, knowledge, individual characteristics, and mobile literacy.Objective 2b. Develop a classifier for the routine identification of ASHAs likely to perform poorly.Aim 3: Understand the factors underpinning successful receipt of calls (are calls received?)Objective 3a. Determine what proportion of calls successfully reach the end-user’s device for Kilkari.Objective 3b. Identify the proportion of content specific to infant feeding and family planning received by end-users for Kilkari.Aim 4. Determine how users are listening to messagesObjective 4a. Determine predictors for exposure to Kilkari content based on user characteristics.Objective 4b. Measure exposure to Kilkari content based on technological and behavioral (end-user engagement) performance.Objective 4c. Develop a classifier for measuring listening levels.Aim 5: Understand optimal message delivery options for maximal impactObjective 5a. Determine message delivery options with the most success in engaging client and assess patterns of listening.Objective 5b. Determine the effect of early listening patterns (time of day of listening, duration and frequency of listening, content listening patterns) on postpartum engagement and overall exposure.

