Area under receiver operating characteristic curve (AUROC)	Area covered by the function of true positive rate/ false positive rate	The curve is plotted and area between the curve and the 45° line is multiplied by 2 to give the AUROC. A value of 1 represents perfect accuracy while 0.5 means the prediction is worthless.

^a^TP: true positive, TN: true negative, FP: false positive, FN: false negative

To illustrate the definition of performance metrics for Mobile Academy, we define true positives (TP) as the number of correctly classified ASHAs who have completed the training, and true negatives (TN) as the number of correctly classified ASHAs who have not completed the training. False positives (FP) are defined as the number of ASHAs incorrectly classified as having completed the training, while false negatives (FN) are the number of ASHAs incorrectly classified as not having completed the training.

Results from the performance metrics will help define the final model for each algorithm. In Step 2, these final models for each algorithm will be applied to the test dataset, which comprises approximately 20% of the total data. Using the same performance metrics, the models with the best fit and accuracy will be applied to the validation dataset as part of Step 3. Ultimately, predictions for Mobile Academy will aim to determine the probability of the ASHA finishing the course in a predetermined time frame and the possible score/performance of the individual ASHAs. For Kilkari, we will determine predictors for exposure to Kilkari content based on user characteristics, as well as explore the effect of early listening patterns on postpartum engagement and overall exposure.

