Analyses to understand the technological performance of the program will build off of those conducted on the MOTECH platform in Ghana [19] and of MomConnect in South Africa [8]. In the former, IVR message delivery trends suggested that 25% or less of expected mobile health information messages were received by pregnant women [19]. While 20% delivery rates of successful outbound dialing calls are standard in the mobile industry, limitations in the timeliness of problem identification represent a missed opportunity for improving program exposure using, for example, call retry logics and systems. In South Africa, over 80% of short messaging service (SMS) messages were successfully delivered as part of MomConnect. SMS as a delivery channel has a much higher success rate than outbound dialing calls but suffers from other weaknesses in countries where illiteracy rates are high and local language fonts are not widely available on devices. In the case of MomConnect, however, challenges in the use of unstructured supplementary service data meant that 26% of initiated registrations did not convert into successful registrants [8]. These two examples reinforce the need to understand the user journey and follow the flow of data to understand whether the technology performs as intended.

Beyond understanding the technological performance of the program, and the wider telecommunications network and device landscape that it operates within, analyses will aim to measure user engagement, including predictors for exposure to content based on user characteristics. In the context of Kilkari, we will additionally plan to explore the effect of early listening patterns (eg, time of day of listening, duration and frequency of listening, content listening patterns) as a predictor for postpartum engagement and overall exposure. For Mobile Academy, we will use a mixture of unsupervised and supervised machine learning techniques to generate predictors of training course completion by ASHAs based on performance on early modules of the course. These will be externally validated using a range of data elements on other ASHA characteristics obtained from the broader evaluation, including reported motivation, knowledge, individual characteristics, and mobile literacy.

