### Limitations

Ethical issues related to identifiers are important considerations for analyses described here. We will de-identify the databases at the point of data download, and all data will be secured in a password-protected hard storage device with access controlled by the Principal Investigator of the study. Once data are accessed, we note that findings will be only as reliable as the quality of underlying data. Completeness of the coverage of data and the data elements can be limited in low-resource settings. In recognition of this challenge, we will assess the quality of data for completeness and timeliness. The inherent design of the messaging program means that only those with mobile phones can be part of the sample, which could introduce selection bias in the association between outcome and predictors. Confounding will be an issue due to the many unmeasured variables associated with exposure such as mobile phone ownership, and registration into the pregnancy tracking database, and outcomes such as active listening to messages and adoption of healthy behaviors. Call answering does not automatically mean listening to the message by the intended client (eg, ASHAs or pregnant women) and as such, our analyses will be limited in its ability to identify the listener (information bias). However, the potential benefits of having other family members listen to information content could be immense. Beyond challenges with the measurement of exposure, the absence of a complete set of predictors will be present due to the limitations of such large-scale data gathering processes (incomplete model).

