### Conclusions

This paper aims to provide a survey of approaches to the applications of machine learning to improve the implementation and evaluation of digital health programs. The two digital health examples described represent two of the largest digital health programs, based on number of active users, currently being implemented globally. Developing classifiers based on the above machine learning approaches will help identify gaps in data (Aim 1), target potential slow learners (Aim 2), measure exposure to program (Aim 3), characterize exposure levels in the population (Aim 4), and evaluate program impact (Aim 5). The scale of implementation and associated generation of data on user engagement with program content provides opportunities for big data analytics and more specifically, the use of machine learning approaches to improve the generation of evidence on program reach and exposure as well as factors underpinning uptake for both Mobile Academy and Kilkari.

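### Objective 5b predicts overall exposure from early listening that overall exposure already includes, so part of any association is arithmetic, and it is worded as an effect

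*Protocol article*

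**What the plan says.** Objective 5b in Textbox 1 (Introduction) names three kinds of early listening pattern as predictors (time of day, duration and frequency, and content) and two outcomes, ending "content listening patterns) on postpartum engagement and overall exposure". Testing and Validation repeats the plan to "explore the effect of early listening patterns on postpartum engagement and overall exposure". Principal Considerations, in the Discussion, again speaks of an effect but in the same sentence treats early listening "as a predictor for postpartum engagement and overall exposure".

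Objective 4b gives the basis for measuring exposure: "Measure exposure to Kilkari content based on technological and behavioral (end-user engagement) performance". Table 1 lists the Kilkari records that would feed it, including calls answered and the duration heard per message. No section states how long the early window is or removes it from overall exposure.

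Table 4 says that an AUROC of 1 is perfect and 0.5 worthless, and Testing and Validation selects models on the Table 4 metrics.

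The Conclusions say that the classifiers will "evaluate program impact (Aim 5". The Limitations state: "Confounding will be an issue due to the many unmeasured variables associated with exposure". The section on additional baseline survey data places the assessment of causality in the separate randomized trial, which has a no-content arm.

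**The concern.** Postpartum engagement is named as its own outcome, so overall exposure most naturally means listening across the whole subscription. Early duration and frequency of listening are then components of the outcome they are asked to predict, and a part correlates with its whole even when nothing carries over from one period to the next.

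Two things follow. First, a model with no information about later behaviour can score above the 0.5 that Table 4 gives as the worthless value, so the article's benchmark misleads for this outcome. Second, the article calls the relation an effect and describes Aim 5 as evaluating impact. Early listening is not randomized, and neither Aim 5 objective compares recipients with non-recipients. A program team given the result could take an accounting identity as evidence that early listening drives later engagement. The confounding caveat in the Limitations does not mention the overlap and does not remove it.

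**Working it through.** The article states no association, sample size or power for Objective 5b, so there is no figure to reproduce. The check asks how large the association would be if early listening told us nothing about later listening.

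**Inputs**
- Message period: weekly, from the second trimester until the child is one year old (Introduction). The number of messages is not stated. Assumption: about 27 antenatal + 52 postpartum = 79.
- Early window: not stated. Values tried: k = 4, 8, 12 and 27 weeks, the last being all antenatal messages.
- Outcome for AUROC: above-median overall exposure (assumption).

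**Formula.** Let E be early listening and L later listening, independent of each other, with total T = E + L. Then

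corr(E, T) = SD(E) / √(Var(E) + Var(L)).

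Two assumptions about week-to-week behaviour, each applied to both periods:
- A, weeks independent with equal variance: r = √(k/79).
- B, listening fully persistent within a period and independent between periods: r = k / √(k² + (79 − k)²).

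Examples for k = 12: A gives √(12/79) = 0.390; B gives 12/√(144 + 4489) = 0.176.

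Both were simulated with 200,000 users per setting. Under A each message was heard with probability 0.5. Under B each user had a uniform listening propensity, drawn separately for each period.

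| Early weeks | r, A | r, B | AUROC, A | AUROC, B |
|---|---|---|---|---|
| 4 | 0.225 | 0.053 | 0.599 | 0.521 |
| 8 | 0.318 | 0.112 | 0.642 | 0.541 |
| 12 | 0.390 | 0.176 | 0.676 | 0.564 |
| 27 | 0.585 | 0.461 | 0.771 | 0.678 |

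The r columns are from the formulas and the AUROC columns from simulation. Simulated correlations were 0.223, 0.317, 0.388 and 0.585 under A. Under B they were 0.064, 0.126, 0.189 and 0.470, slightly above the formula because sampling of individual messages adds some week-level noise.

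**Message count.** With 78 messages instead of 79, scenario A gives √(12/78) = 0.392 and √(26/78) = 0.577, so the result does not turn on the exact total.

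**Later-only outcome.** Replacing T by L in the same simulations gives correlations between −0.004 and 0.004 and AUROC between 0.499 and 0.501 for every window. The artefact disappears, and 0.5 is again the correct null.

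**The case against.** The strongest reply is that the article never defines overall exposure as a sum over the whole subscription, and that exact windows and outcome definitions belong in a fuller plan. That is fair as to the missing window length, which is not the complaint here. It does not dispose of the point: the article names overall exposure as distinct from postpartum engagement in three places, and the plain meaning of that pairing includes the early weeks.

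A second reply is that forecasting total exposure from early listening is a legitimate operational task. It is, but the forecast then earns credit for listening already recorded, 0.5 is not its null, and it is not evidence of an effect.

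A third is that the causal language is mild. Testing and Validation says explore, Principal Considerations also says predictor, and causality is left to the randomized trial. This softens the wording point. It also shows that the words effect and impact sit badly with the rest of the article.

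Some stronger readings are tempting but not supported:
- A reader might infer that a strong association is guaranteed. With a short window and persistent listening, the built-in correlation is close to nil.
- A reader might infer that all of Objective 5b fails. Postpartum engagement does not overlap with early listening if early means antenatal, and time of day and content are not summands of total listening.
- A reader might infer that dropout is ignored. Aim 1 is devoted to subscriber losses, and the article does not rule out restricting the analysis to women still subscribed.
- A reader might attach the impact label to Objective 5b itself. The Conclusions attach it to Aim 5 as a whole.

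**Conclusion.** The point holds for one of the two outcomes in Objective 5b, and mainly for the duration and frequency predictors. As worded, overall exposure contains its predictor, so part of any association is arithmetic and an AUROC of 0.5 is not the no-information value.

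The size cannot be fixed from the article. Under no carry-over it runs from r of about 0.05 and AUROC 0.52 to r of about 0.58 and AUROC 0.77. If early means the whole antenatal period, a natural but unstated reading, the range narrows to r = 0.46 to 0.58 and AUROC 0.68 to 0.77, which is not negligible.

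These figures assume about 79 messages, the full message schedule for every user, a median split, and the same persistence in both periods. Scenarios A and B are contrasting cases rather than formal bounds, and unequal variability between the periods could fall outside them. The direction does not depend on these choices.

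The words effect and impact go beyond what the analysis can show, since Aim 5 has no unexposed comparator and the article concedes unmeasured confounding.

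**What to change.** 1. In Objective 5b, and in the matching sentences in Testing and Validation and Principal Considerations, replace overall exposure with exposure accrued after a stated early window: the share of messages due after that window that were heard.
2. In the same places, describe the result as a predictive association instead of an effect.
3. In the Conclusions, change the description of Aim 5 from evaluating impact to predicting later engagement, and leave impact to the randomized trial.

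This matches the Abstract, which already speaks of linking early listening to continued engagement. The cost is one outcome definition and a few words. The reported predictive strength will be smaller. If the early window is set to the whole antenatal period, the new outcome will lie close to postpartum engagement; a shorter window keeps the two more distinct.

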## Results

The project has obtained the necessary approvals for the use of data in accordance with global standards for handling personal data. The results are expected to be published in August 2019.

## Discussion

### Principal Considerations

This paper presents the testing of a range of machine learning approaches to be incorporated as part of the evaluation of two large digital health programs in India—Mobile Academy and Kilkari. By utilizing machine learning approaches, we aim to improve the use of data for generating evidence on program reach and exposure as well as factors underpinning uptake for both programs. We will start by measuring dropped cases and missing data along the continuum of the databases. As part of this analysis, we aim to understand differentials in the characteristics of individuals lost along the continuum of databases and in turn, missed by the Mobile Academy or Kilkari programs. We then consider the technological performance as captured by four stakeholders: (1) government data systems (MCTS, RCH, webservices), (2) program’s call delivery and receipt systems, (3) mobile network operator (network coverage and quality), and (4) user device characteristics (switched on, within range of network). Finally, we explore user engagement with the program (behavioral performance) including patterns in the data that could predict key program performance metrics, including training completion for Mobile Academy and user coverage and exposure for Kilkari.

Analyses to measure dropped cases and missing data along the continuum of the databases, starting with the MCTS and RCH databases, are anticipated to generate insights into user relay of information to the Government of India including the provision of phone numbers by health workers and women. At present, there are no reliable estimates of the proportion of pregnant women with accurate mobile numbers, last menstrual periods, or dates of birth (for themselves or child) covered by the databases. More broadly, these analyses will help improve understanding of the quality of the RCH and MCTS data and underlying sampling frames used for Mobile Academy, Kilkari, and a range of other programs, including the characteristics of individuals included compared to those excluded. The predictors identified will help identify groups of women who are more likely to be missed by the program and ASHAs less likely to complete their course. These findings will also be used to inform the sampling of respondents for qualitative research to explore issues in depth and possibly identify opportunities for improving program targeting like registration of users.

Analyses to understand the technological performance of the program will build off of those conducted on the MOTECH platform in Ghana [19] and of MomConnect in South Africa [8]. In the former, IVR message delivery trends suggested that 25% or less of expected mobile health information messages were received by pregnant women [19]. While 20% delivery rates of successful outbound dialing calls are standard in the mobile industry, limitations in the timeliness of problem identification represent a missed opportunity for improving program exposure using, for example, call retry logics and systems. In South Africa, over 80% of short messaging service (SMS) messages were successfully delivered as part of MomConnect. SMS as a delivery channel has a much higher success rate than outbound dialing calls but suffers from other weaknesses in countries where illiteracy rates are high and local language fonts are not widely available on devices. In the case of MomConnect, however, challenges in the use of unstructured supplementary service data meant that 26% of initiated registrations did not convert into successful registrants [8]. These two examples reinforce the need to understand the user journey and follow the flow of data to understand whether the technology performs as intended.

Beyond understanding the technological performance of the program, and the wider telecommunications network and device landscape that it operates within, analyses will aim to measure user engagement, including predictors for exposure to content based on user characteristics. In the context of Kilkari, we will additionally plan to explore the effect of early listening patterns (eg, time of day of listening, duration and frequency of listening, content listening patterns) as a predictor for postpartum engagement and overall exposure. For Mobile Academy, we will use a mixture of unsupervised and supervised machine learning techniques to generate predictors of training course completion by ASHAs based on performance on early modules of the course. These will be externally validated using a range of data elements on other ASHA characteristics obtained from the broader evaluation, including reported motivation, knowledge, individual characteristics, and mobile literacy.

Overall, the proposed analyses are anticipated to complement primary data collection activities proposed as part of the summative evaluation of Kilkari and Mobile Academy. Findings emerging from this analysis will provide program implementers with tools for improving predictions of success and performance and provide insights into strategic use and collection of data. Elsewhere, deployments of similar programs including MomConnect in South Africa, Aponjan in Bangladesh, as well as other maternal messaging programs may be able to apply some of the same approaches described [8].

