**Methods:**

Study participants include pregnant and postpartum women (Kilkari) as well as frontline health workers (Mobile Academy) across 13 states in India. Data elements are drawn from system-generated databases used in the routine implementation of programs to provide users with health information. We explain the structure and elements of the extracted data and the proposed process for their linkage. We then outline the various steps to be undertaken to evaluate and select final algorithms for identifying gaps in data quality, poor user performance, predictors for call receipt, user listening levels, and linkages between early listening and continued engagement.

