### Additional Data From Baseline Surveys of Evaluation of Kilkari and Mobile Academy

Analyses described in this section are being carried out as part of a larger external evaluation of Kilkari. We describe concurrent efforts to undertake a randomized controlled trial (RCT) in the state of Madhya Pradesh (MP) for Kilkari, inclusive of baseline surveys with pregnant and postpartum women, and ASHA workers. Once identified as part of baseline survey activities and randomized to receive Kilkari content (or no content at all), phone numbers will be fed directly into the MOTECH database for provision of program services. For pregnant women, additional data collected as part of baseline household surveys include demographic factors (age, education, parity, literacy), socioeconomic characteristics (household assets, conditions), health care seeking and practices, as well as data on digital literacy and phone access. These data can be linked to MOTECH, IVR, and call center records to provide additional data elements. Overall, these data as well as data on technology performance (receipt of messages) and user engagement (behavioral performance) with content will help estimate exposure to Kilkari used in the assessment of causality as part of the RCT. For ASHAs, baseline survey data will include similar data elements on demographic, socioeconomic, and mobile literacy and phone access as well as knowledge and work-related variables linked to reported motivation and satisfaction. Overall, these added data elements can be linked to IVR and call record data for this subpopulation of Mobile Academy and Kilkari users in four districts of MP where the RCT is underway.

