**Supervised**				
	1 Logistic regression	Classification (nonlinear model)	Classification of ASHA workers by user characteristics and patterns of training initiation by ASHAs	User characteristics associated with exposure to messaging content and duration in MP where face-to-face survey data have been collected
	2 Linear discriminant analysis	Classification (linear model). It is a linearization of Gaussian naïve Bayes.	Classification of ASHA workers by user characteristics and patterns of training initiation, completion, and performance	User characteristics associated with exposure to messaging content and duration
	3 Support vector machines (SVMs)	SVMs are techniques based on the calculation of the maximum margin hyperplane for the classification problems	Classification of ASHA workers by user characteristics and patterns of training initiation and completion	User characteristics associated with exposure to messaging content and duration
	4 Classification and regression trees	Predictive model that consists of leaves that represent the target and branches that represent conjunctions of inputs features. Considered a subset of decision trees. Random forests operate by constructing multiple decision trees during training and aggregating their results to avoid overfitting by single trees.	Classification of ASHA workers by user characteristics and patterns of training initiation and completion	User characteristics associated with exposure to messaging content and duration
	5 Naïve Bayes	Classification model based on probabilities	Classification of ASHA workers by user characteristics and patterns of training initiation and completion	User characteristics associated with exposure to messaging content and duration
	6 Neural Networks (NNs)	NNs are powerful models for machine learning. They are a generalization of linear and nonlinear models	Classification of ASHA workers by user characteristics and patterns of training initiation and completion	User characteristics associated with exposure to messaging content and duration

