### Testing and Validation

To facilitate decision making on the optimal analytic approach, three steps will be undertaken: (1) develop the correct model for each algorithm using the training dataset, (2) apply the final model for each algorithm on the test dataset, and (3) apply the best performing algorithm on the validation dataset.

In Step 1, algorithms will be run using the training dataset comprising 60% of the total sample from across all states for which data are available. For each algorithm, iterative testing will be run to select the best model that fits the data. The emerging results will then be assessed for model fit and accuracy. Table 4 summarizes the four proposed metrics for assessing the performance of each model.

**Table 3 table3:** Performance comparisons of learning algorithms modified from Kotisiantis et al [17,18] (++++ represents the best and + the worst performance).

Model attributes	Decision trees	NNs	Naïve Bayes	SVM	Linear discriminant analysis	Logistic regression
Accuracy in general	++	+++	+	++++	+++	++
Speed of learning with respect to number of attributes and number of instances	+++	+	+++	+		
Speed of classification	++++	++++	++++	++++	++++	++
Tolerance to missing values	+++	+	++++	++	+++	+
Tolerance to irrelevant attribute	+++	+	++	++++	+++	+
Tolerance to redundant attributes	++	++	+	+++	++	+
Tolerance to highly interdependent attributes	++	+++	+	+++	++	+
Dealing with discrete/ binary/ continuous attributes	++++	+++ (not discrete)	+++ (not continuous)	+++ (not discrete)	++++	+++
Tolerance to noise	++	++	+++	++	+++	++
Dealing with danger of overfitting	++	+	+++	++	++	+
Attempts for incremental learning	++	+++	++++	++		
Explanation ability/ transparency of knowledge/ classification	++++	+	++++	+	+	+
Model parameter handing	+++	+	++++	+	++	+

**Table 4 table4:** Metrics for assessing the performance of each model.

Model metrics	Formula^a^	Description
Accuracy	(TP+TN)/(TP+TN+FN)	Proportion of cases correctly classified
Precision or positive predictive value	TP/(TP+FP)	Fraction of relevant instances among the retrieved instances
Sensitivity or recall	TP/(TP+FN)	Fraction of relevant instances retrieved over total amount of relevant instances

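### The ASHA survey items offered as external validation are also Objective 2a predictors, and, separately, Table 2 confines only the Kilkari logistic regression to Madhya Pradesh

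*Protocol article*

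**What the plan says.** **Mobile Academy.** Objective 2a (Textbox 1, Study aims) sets out to predict course completion from early-module performance and "other characteristics including reported motivation, knowledge, individual characteristics, and mobile literacy". In the Discussion (Principal Considerations), predictors of completion are generated from early-module performance, and then: "These will be externally validated using a range of data elements on other ASHA characteristics obtained from the broader evaluation". The elements meant are described as "obtained from the broader evaluation, including reported motivation, knowledge, individual characteristics, and mobile literacy".

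The Methods section on additional baseline survey data says that the ASHA survey will collect demographic, socioeconomic and phone-related items as well as "knowledge and work-related variables linked to reported motivation and satisfaction". It treats these as added elements that can be linked to call records for a "subpopulation of Mobile Academy and Kilkari users in four districts of MP where the RCT is underway". The programs as a whole are studied "across 13 states in India".

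**Kilkari.** In Table 2 the intended Kilkari application of logistic regression is user characteristics associated with exposure to content and "duration in MP where face-to-face survey data have been collected". The other five supervised rows have no such limit. Step 1 of Testing and Validation trains the algorithms on "60% of the total sample from across all states", subject to data being available. Steps 2 and 3 compare the final model of each algorithm on the test set with common metrics and carry the best forward to the validation set.

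**The concern.** These are two separate points, about different programs.

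For Mobile Academy, one set of variables has two roles that cannot both hold: input to the completion model, and the external standard against which that model is checked. External validation means applying a fixed model to people, places or periods that were not used to build it. Further columns on a subset of the same users do not provide that. At stake is a claim of transportability that has not been tested, in a paper that suggests similar programs elsewhere may apply the same approaches.

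For Kilkari, if both Table 2 and the Testing and Validation section are followed, logistic regression would be judged on one state's surveyed users, probably with richer predictors, and its competitors on all available states. Its position in the comparison would then mix differences in data with differences in method.

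**Working it through.** The article gives no figure to reproduce here. The check is mainly a comparison of texts, with one small calculation.

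**1. Do the two variable lists match?**

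| Item | Objective 2a (predictor) | Principal Considerations (validation) |
|---|---|---|
| Reported motivation | yes | yes |
| Knowledge | yes | yes |
| Individual characteristics | yes | yes |
| Mobile literacy | yes | yes |

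All four match, in the same order.

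**2. Are the surveyed ASHAs a new sample?** The baseline survey section describes linkage to call records for a subset of current users. Nothing in the article keeps these ASHAs out of training. The split is 60/20/20 (Splitting Into Training and Testing), by random sampling with balance over time periods.

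**3. Expected overlap with model building.** Let f be the share of surveyed ASHAs who are in the extracted data, and assume a random split by ASHA.

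- In training: 0.60 × f.
- In training plus test, the test set also being used for fine-tuning: (0.60 + 0.20) × f = 0.80 × f.
- With f = 1: 60% and 80%, leaving 20% in the validation set.
- With f = 0.5: 30% and 40%.
- With f = 0: no overlap, but then there would be no linked outcome in the extract to validate against.

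The article gives neither f nor the unit of the split. If records rather than ASHAs were split, overlap would be higher: an ASHA with two independently assigned records has at least one in training with probability 1 − 0.4² = 0.84.

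**4. What validation remains?** The 20% validation set is drawn at random from the same states and years as the training set. It is an internal hold-out for both programs, and neither point here affects it.

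**5. Table 2 against Testing and Validation (Kilkari).** One of six supervised algorithms, logistic regression, is limited to MP survey data; 6 − 1 = 5 are not. Step 1 trains on all states with available data, and Steps 2 and 3 select on the same metrics, with no exception stated for logistic regression. The Mobile Academy cell for logistic regression has no MP limit, so this conflict belongs to Kilkari only.

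**The case against.** The strongest defence of the Mobile Academy sentence is that it uses the term loosely, for a check against data from outside the program databases. It is also one sentence in the Discussion of a condensed article. That may explain the wording, but Objective 2a still assigns the same items to the model, so the two places need to be reconciled.

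For Kilkari, Table 2 lists intended applications, and the article says that methods will be chosen by their strengths and by the objective. A logistic model of survey characteristics in MP could be a separate analysis. The condition that data be available also softens the conflict. This stands in part: no text says outright that an MP-only model will be ranked against all-state models. But none says that it will not be, and the selection procedure is written for all algorithms.

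Three stronger readings are tempting and are not supported:

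- A reader might infer that neither the validation nor the algorithm comparison is valid. The 20% test and 20% validation sets remain, and the other five Kilkari algorithms are unaffected.
- A reader might infer that the routine classifier of Objective 2b cannot be used outside MP. Objective 2b does not say that it needs survey variables. Chapter-wise scores are in the MOTECH database (Table 1), and ASHA age and location are in routine records (Data Processing).
- A reader might take the 60% and 80% overlap as established. It depends on the assumptions in the working.

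**Conclusion.** Both points hold in limited form.

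For Mobile Academy, the article promises an external validation that its described data do not deliver. This assumes that the broader evaluation is the baseline survey; the shared content (ASHA motivation, knowledge, mobile literacy) supports that, but the article does not state it. The overlap of about 60% with training, and 80% with training plus test, is an expectation. It holds only if all surveyed ASHAs are in the extract and the split is random by ASHA. The mislabelling does not depend on those percentages.

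For Kilkari, one Table 2 cell is at odds with the all-states training and common-metric selection. The effect is confined to where logistic regression would rank, and arises only if the MP-only model enters the ranking.

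**What to change.** **Mobile Academy.** Either remove the external-validation wording from Principal Considerations, or make it true: leave whole states out of fitting and report AUROC in each left-out state. State the role of the survey variables once. The natural place is an MP sub-study that reports their added predictive value over the model based on system data alone, in the same ASHAs.

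**Kilkari.** Reconcile the logistic regression cell in Table 2 with Testing and Validation, so that every supervised algorithm being ranked is fitted and tested on the same records, predictors and outcome. Report any MP survey model as a separate comparison outside the ranking.

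**Cost.** Changes of wording in two places and some refitting on data already held, with no new data collection. The downside is that performance in left-out states may be less favourable than in the random hold-out.
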